## Abstract

**Background:**

Perinatal depression, especially minor depression, is common during pregnancy and is likely to continue into the postpartum period. It may impair the mother’s health, the infant’s neurodevelopment, and the mother-infant relationship. Screening for perinatal depression is recommended; however, there is no consensus on how to treat depressive symptoms while simultaneously supporting the mother-infant relationship. Ultrasound examination has been shown to improve maternal-fetal attachment among pregnant women. Our aim is to develop a four-dimensional (4D) based interactive ultrasound intervention and test whether it relieves minor depressive symptoms and improves maternal-fetal attachment. Previous studies show that supporting the mother-infant relationship aids in relieving maternal depression. Until now, few studies have combined pregnancy ultrasound and psychological support.

**Methods:**

A controlled randomized setting was designed to assess whether interactive 4D-ultrasound intervention would decrease maternal depressive symptoms, strengthen maternal-fetal attachment, and mother-infant relationship. An obstetrician and a psychologist specialized in infant mental health conduct the interventions. The focus is to jointly observe the behavior of the fetus according to the mothers’ wishes. Altogether, 100 women scoring 10–15 on Edinburgh Pre-/Postnatal Depression Scale (EPDS) and with singleton pregnancy are recruited using a web-based questionnaire. Half of the participants will be randomized to the intervention group and will undergo three interactive ultrasound examinations. The primary outcomes are a decrease in perinatal depressive symptoms assessed with EPDS and an increase in maternal attachment. The maternal attachment was assessed using the Working Model of the Child Interview (WMCI), the Maternal Antenatal Attachment Scale (MAAS), and the Maternal Postnatal Attachment Scale (MPAS). Secondly, we hypothesize that if the intervention decreases prenatal depressive symptoms and improves prenatal attachment, the decrease in depressive symptoms and improvement in mother-infant relationship is seen postnatally.

**Discussion:**

Ultrasound is widely used during pregnancy. The interactive approach is unique and may be feasible as part of routine screenings and maternity clinic visits. Intervention that decreases depression and simultaneously supports maternal-fetal attachment would be a valuable addition to the treatment of minor depression among pregnant women.

**Trial registration:**

ClinicalTrials.gov NCT03424642. Registered on January 5 2018.

## Administrative information

Note: the numbers in curly brackets in this protocol refer to SPIRIT checklist item numbers. The order of the items has been modified to group similar items (see http://www.equator-network.org/reporting-guidelines/spirit-2727-statement-defining-standard-protocol-items-for-clinical-trials/).

## Introduction

### Background and rationale {6a}

Perinatal depressive symptoms are a significant health problem affecting both mothers’ and infants’ well-being. According to systematic reviews, the global prevalence of perinatal depression varies between 8.5 and 11.9% [1, 2]. The incidence in the Finnish population is between 7 and 13% [3–5] and is 14.5% internationally [6]. The use of different instruments and cut-off points to assess depression may explain the varying results [7]. In a Finnish cohort sample, 24% of pregnant women reported moderate levels of depressive symptoms throughout their pregnancy [8]. The prevalence of minor depression during pregnancy has not been studied as systematically as major depression, even though minor depression may be more common [9, 10]. Maternal depressive symptoms during pregnancy tend to remain stable and continue into the postpartum period [1, 11–15].

Maternal perinatal depressive symptoms have an adverse effect on the early mother-infant relationship through three components: pre- and postnatal attachment, mental representations and parent-infant interaction behavior. Maternal prenatal depressive symptoms have a negative association with attachment to the unborn infant [13, 16–19], which, in turn, predicts low maternal involvement in the mother-infant interaction [20, 21]. Prenatal depressive symptoms have also been shown to be risk factors for suboptimal postnatal maternal attachment [13, 22]. It has been found that pregnant women at the most risk of low levels of attachment are depressed and have negative feelings toward the upcoming birth and parenthood [19]. Furthermore, various studies have shown that prenatal depression distorts the mothers’ representation of the infant and their own upcoming motherhood, which, in turn, predicts dysfunctional postnatal mother-child interaction [23–25]. Prenatal representations of pregnant women have been shown to remain quite stable from pregnancy to the postnatal period [26–28]. Maternal depression predisposes the infant to several adverse neurodevelopmental risks [29–31]. A Finnish longitudinal study suggests an additive effect of maternal pre- and postnatal depressive symptoms on child neurodevelopment [32].

The fetal effects of antidepressant medication used during pregnancy should be taken into account. For example, fetal exposure to selective serotonin reuptake inhibitors (SSRIs), which are commonly used antidepressants [33], is associated with neonatal maladaptation [34] and increased rates of depression in early adolescence [35]. The literature has consistently highlighted the importance of identifying women at risk of perinatal depression by screening depressive symptoms and determining effective and individual prevention strategies [11, 25, 36, 37]. However, a decrease in a mother’s depressive symptoms alone does not necessarily improve parenting or the infant’s well-being [38–41]. Some evidence indicates that relationally focused treatments may be more effective than traditional treatments in treating maternal depression [38, 42]. Supporting the mother-infant relationship makes it possible to decrease maternal depression [13, 43, 44]. Thus, early interventions supporting the mother-infant relationship or parenting should be available in primary health care [45, 46] and should start before birth to improve the child’s subsequent development of the child [43, 47].

Ultrasound examinations have a beneficial impact on maternal-fetal attachment [48–51] in low-risk pregnancies. Especially, three-dimensional (3D) and four-dimensional (4D) ultrasounds can enhance mental images about the fetus and increase bonding [52, 53]. There are few studies on combining pregnancy ultrasound and psychological support [54–59]: these interventions are based on an ultrasound consultation method, where the fetus is observed with the mother-initiated interaction [54]. A study involving a small group of women with low-risk pregnancies found that participation in ultrasound consultation could improve maternal attachment and decrease general anxiety symptoms [55]. Intervention in parenting using interactive 4D ultrasound with a focus on mentalization among substance-abusing pregnant women showed high attendance in intervention visits compared with routine care [58]. The way in which ultrasound examinees comment on and interpret the ultrasound images and fetal actions influences parents’ prenatal mental representations of the fetus [60]. Routine ultrasound examinations provide pregnant women a step toward parenthood and a possibility to see the fetus [61] and reduce their worried state of mind [62].

Using interactive ultrasound, we conducted a qualitative study to map the experiences of women at risk of preterm birth. The pregnant women’s experience of the intervention was that it made the fetus more real, strengthening their feelings of attachment to their fetus [59]. The interactive ultrasound intervention has the potential to strengthen maternal prenatal attachment and representations and decrease anxiety and depression. Pregnancy ultrasound may thus be used as a tool for assessing fetal risks, but also an instrument in prenatal psychological interventions.

### Objectives {7}

#### Aim

The primary aim of the present study is to evaluate, whether interactive ultrasound decreases perinatal depressive symptoms by increasing maternal attachment. The secondary aim is to evaluate whether interactive ultrasound improves also postnatal mother-infant interaction.

The specific hypotheses are as follows:
The intervention decreases prenatal depressive symptoms and improves the attachment to the fetus.
The mothers in the intervention group will have fewer depressive symptoms after intervention than before the intervention.The decrease in depressive symptoms will be greater in the intervention group than in the control group.The improvement of prenatal attachment from the pre-intervention to the post-intervention time will be greater in the intervention group compared with the control group.The mothers in the intervention group will have a more balanced attachment representation after the intervention than before the intervention.The change from non- balanced to balanced attachment representations will be greater in the intervention group than in the control group.If the intervention decreases prenatal depressive symptoms and improves prenatal attachment, the effect prevails postnatally and improves mother-infant interaction.
The decrease in the depressive symptoms remains in the intervention group 4 to 5 months old.The mothers in the intervention group will have a stronger attachment to their infant when the child is 4 to 5 months old.The quality of mother-infant interaction will be higher in the intervention group than in the control group when the child is 4 to 5 months old.

Moreover, we will explore the effect of the intervention on various forms of maternal psychological distress. However, too little is known about the trajectories of pregnancy-related anxiety in low-risk populations to state a hypothesis about this. For perinatal outcomes such as preterm birth (< 37 gestational weeks, [gwks]), intrauterine growth restriction (IUGR), and low (< 2.5 kg) birth weight at delivery, the power of the sample is likely to be too low to gain significant differences between groups.

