### Eligibility criteria {10}

The inclusion criteria are as follows:(1) 10–15 points on the EPDS, (2) singleton pregnancy, (3) over 18 years of age, (4) body mass index under 35, and (4) fluency in the Finnish language.

The exclusion criteria are psychotic and self-destructive symptoms. The use of antidepressant medication is not an obstacle to participation.

The women are recruited after the routine screening for severe structural abnormalities between 19 and 21 gwks offered by the municipalities. Severe structural abnormalities are an exclusion criterion.

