### Methods for additional analyses (e.g., subgroup analyses) {20b}

The sample size and the subgroups are small. Preliminary analyses are conducted to find out if there are statistically significant differences within and between the study groups.

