## Discussion

Nonmedical and early relationship-focused therapies should be available to treat prenatal depression because supporting the mother-infant relationship makes it possible to decrease depressive symptoms, improve the subsequent development of the child, and avoid the negative effects of antidepressant medication on infants’ health [13, 34, 35, 43–46]. Psychotherapeutic and psychosocial interventions are effective in treating perinatal depression [91] but require special expertise and resources. Moreover, the reduction in a maternal depressive symptoms alone may not improve parenting or the infant’s well-being [38–41]. Because fetal ultrasound has been considered a promising method to support maternal-fetal attachment [92], an ultrasound-assisted intervention could be a low-threshold type of support and easily feasible in maternity care. Therefore, an ultrasound examination used in an interactive manner may be a potential and cost-effective way to support pregnant women with minor or moderate depressive symptoms.

The strengths of our study are the mixed methods and the longitudinal approach that continues into the postpartum period. Furthermore, the multiprofessional approach enables the support of pregnant women in various ways. A weakness in our randomized controlled trial may be the control group’s participation in the attachment representation interviews, which can be experienced as an intervention itself.

Our aim is to develop an intervention for pregnant women with depressive symptoms using 4D ultrasound in an interactive way. The interactive approach is unique and could be integrated into maternity care with a moderate investment. The core elements of the intervention listening to the mother, personalizing the fetus, and giving emotional support can easily be implemented during routine screening and maternity clinic visits. This intervention could serve as a means for maternity care to help women suffering from minor perinatal depression.

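### Two prenatal hypotheses are before-after comparisons within the intervention arm and the postnatal EPDS hypothesis names no control comparison, so they could be called confirmed with no between-group difference

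*Protocol article*

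**What the plan says.** Objectives {7} of the protocol article lists specific hypotheses about the effect of the intervention. Three concern the intervention arm alone or name no comparator:

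- Prenatal EPDS: "The mothers in the intervention group will have fewer depressive symptoms after intervention than before the intervention".
- Prenatal representations (WMCI): "The mothers in the intervention group will have a more balanced attachment representation after the intervention than before the intervention".
- Postnatal EPDS: "The decrease in the depressive symptoms remains in the intervention group 4 to 5 months old".

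The same list gives between-group companions for the first two: "The decrease in depressive symptoms will be greater in the intervention group than in the control group" and "The change from non- balanced to balanced attachment representations will be greater in the intervention group than in the control group". It gives none for postnatal EPDS.

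The statistical methods section {20a} tests EPDS change through the interaction of time point and intervention in a mixed model. It also estimates group differences at each time point and within-group changes, and sets one general two-tailed criterion of P below 0.05. The section on additional analyses {20b} plans preliminary analyses for "statistically significant differences within and between the study groups".

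Women enter on a web screening score ("10–15 points on the EPDS, (2) singleton pregnancy"). The EPDS is then completed again in REDCap in connection with the first interview, and randomisation follows that interview. Other support or therapy is allowed {11d}. The Discussion says of the interviews, which both arms receive, that they are something "which can be experienced as an intervention itself".

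**The concern.** A before-after change in one arm mixes any effect of the ultrasound visits with everything else that happens between about 25 and 33–35 gestational weeks. The article itself names several such things: other treatment, repeated interviews that may act as treatment, and entry on a raised score. Only the control arm separates these from the intervention.

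The three statements are listed as hypotheses about the intervention's effect, not as descriptive summaries. Read literally, an EPDS fall in the intervention arm would confirm the first one even if the control arm fell equally. The persistence statement could likewise be met if scores stayed low in both arms. The report could then claim that the intervention lowers symptoms, and that the lowering lasts, beside a null randomised comparison.

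**Working it through.** **1. Hypotheses set against their comparators**

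| Hypothesis in {7} | Comparator named | Between-group companion in {7} |
|---|---|---|
| EPDS lower after than before | none | yes |
| Representations more balanced after than before | none | yes |
| EPDS decrease remains at 4–5 months | none | none; {20a} does estimate the group difference at each time point |

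**2. Inputs**

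From Sample size {14}: 50 per group, SD 3.5, a clinically relevant decrease of 3 points, two-sided 0.05. The 50 is taken as stated. It does not follow from the other inputs at 80% power: 2 × (1.96 + 0.84)² × 3.5² / 3² ≈ 21.4, so 22 per group (23 by the t distribution). That is a separate matter.

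Assumption: 3.5 is used as the SD of change. The article calls it the SD of the EPDS score. The two agree if the before-after correlation is 0.5, because 3.5 × √(2 × (1 − 0.5)) = 3.5.

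**3. Smallest fall that reaches significance within one arm**

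SE = 3.5/√50 = 0.495. The critical t on 49 df is 2.010. The smallest significant fall is 2.010 × 0.495 = 0.99 points, about one third of 3.

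**4. Chance of a significant within-arm fall with no intervention effect**

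The noncentrality is drift/0.495, and the probability is that a noncentral t on 49 df exceeds 2.010.

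| Drift common to both arms | Noncentrality | Significant fall |
|---|---|---|
| 0 | 0 | 2.5% |
| 0.5 | 1.01 | 17% |
| 1.0 | 2.02 | 51% |

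With an SD of change of 4.0, a 1.0-point drift gives 41%.

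**5. How much regression to the mean is left after the re-measured baseline**

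This was simulated with no intervention effect, selection on a screening score of 10–15, and 50 per arm. Population mean 5–7, SD 3.7–4 and correlation 0.5–0.8 were used. The means and correlations are assumptions that the article does not give; the SD range is the one it cites.

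Example: mean 6, SD 4, correlation 0.6, mean screening score 11.48.

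- Expected re-measured baseline: 6 + 0.6 × 5.48 = 9.29 (simulated 9.28). The fall of about 2.2 points comes before randomisation and is outside the before-after contrast.
- Equal correlation across times: expected post score again 9.29, no further fall. The within-arm test shows a significant decrease in 2.6% of trials.
- Correlation decaying to 0.36 between screening and post: 6 + 0.36 × 5.48 = 7.97 (simulated 7.99), a further fall of about 1.3 points. The within-arm test is significant in 72.5% of trials.

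Over all settings with the re-measured baseline and no natural decline, the within-arm rate of significant decreases is 2–3% with equal correlation and 54–89% with decaying correlation. In the example setting with equal correlation, a natural decline of 0.5 or 1.0 point gives 16% or 48%. The between-group test rejects in about 4–6% throughout.

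**6. Representations**

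Selection was on EPDS, not on WMCI class, so regression to the mean acts only indirectly. Natural course, repeated interviewing and incomplete blinding of the coders {17a} are the likelier sources of a before-after shift. The article gives no figures from which to size it.

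**The case against.** The trial does not rest on the within-arm statements. Each prenatal one is followed directly by a between-group companion, the sample size section frames the study as a comparison of changes between two groups, and the interaction test is the right one. A reader might infer that the plan abandons randomisation, or contains a rule by which a within-arm fall proves efficacy. It does not: no such rule is written, {20a} speaks of estimating within-group changes, and its P < 0.05 sentence is general. The reference to significance within groups in {20b} belongs to preliminary additional analyses.

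The postnatal statement sits under a condition that the prenatal effect has been shown. EPDS is collected in both arms at 4–5 months, and the group difference at that time will be estimated.

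A reader might also infer that selection on a raised screening score guarantees a spurious fall. The re-measurement before randomisation removes much or all of that, and the background section describes prenatal symptoms as tending to stay stable.

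All of this stands, and it limits the point to how the hypotheses are framed. It does not dispose of it. The within-arm statements remain separate hypotheses of effect, postnatal EPDS has no between-group hypothesis, and general stability of symptoms does not exclude a mean drift of about 1 point in women enrolled on raised scores.

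**Conclusion.** The point holds as a defect in how the hypotheses are framed. The randomised analysis is intact. Two prenatal hypotheses and the postnatal EPDS hypothesis could be declared confirmed with no difference between the arms. For prenatal EPDS, a shared drift of 1.0 point would make the within-arm test significant in about 51% of trials, given an SD of change of 3.5 and n = 50. The rate is near nominal if there is no drift and correlation is equal across times. The article does not settle where between these the trial lies, because the size of any drift and the pattern of correlation are assumptions. For the WMCI statement the conclusion is qualitative only.

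**What to change.** In Objectives {7} and the statistical methods {20a}:

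1. State that conclusions about efficacy rest only on between-group contrasts. The companion hypotheses for prenatal EPDS change and for change in representations already serve this.
2. Add an explicit between-group hypothesis for EPDS change from baseline to 4–5 months.
3. Relabel the within-arm statements as descriptive, and report within-arm changes with confidence intervals for both arms. Make the wording in {20b} consistent with this.
4. State that the baseline is the pre-randomisation REDCap EPDS at the first interview, not the web screening score.

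The cost is a change of wording, with the ethics committee acceptance that {25} requires for protocol changes. No new data, visits or participants are needed, and the mixed model already supplies the estimates.

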### Trial design {8}

The study design is a randomized controlled trial utilizing an intervention group and a control group. Only the intervention group will participate in three interactive ultrasound examinations. All the data collection measures will be done for both intervention and control groups. Also, the attachment representation interviews about their mental health representation of their unborn baby and relationship with the baby will be done twice during the pregnancy for both groups. The trial design is described in the research chart (Appendix 1).

Pregnant women with depressive symptoms are recruited by an advertisement shared on social media by the women’s clinic of Turku University Hospital and by brochures distributed at routine ultrasound scans. The advertisement includes a link to an electronic Edinburgh Pre-/Postnatal Depression Scale (EPDS)-questionnaire. The research team’s doctoral student contacts by phones eligible women, who have provided their contact information, to recruit them.

Those women who agreed to participate in will receive informed consent and the first set of questionnaires by e-mail. During this first contact, the research doctor also schedules the first attachment representation interview with the participants and does a clinical interview to assess the severity of depression. The informed consent forms are signed and collected before starting the first attachment representation interview.

The attachment representation interviews are conducted twice with all the participants between 25 and 35 gwks. Randomization to intervention and follow-up groups occurs after the first attachment representation interview. The participants in the intervention group will receive three interactive ultrasound examinations.

The mother-infant interaction is video-recorded from all participants when the baby is 4–5 months of age.

Background information is collected by means of an electronic questionnaire during the first study visit. Information about depressive and anxiety symptoms, as well as feelings of attachment, is collected by means of electronic questionnaires at three time points: in connection with the attachment representation interviews during pregnancy and the interaction observation visit when the baby is 4–5 months old. The information about the participants’ previous psychiatric diagnoses and pregnancy data are collected from electronic medical records. Prenatal care continues as usual.

